#### Electronic Health Record Chart Review for Ascertainment and Adjudication of Outcomes and Other Variables

A total of 2 study investigators will independently review the medical record 6 months after the initial presentation of the case to ascertain the final diagnosis and exclude cases with persistent diagnostic uncertainty after 6 months. We will resolve discrepancies in adjudication by consensus. Our chart review will also capture the number of comorbid conditions (based on the problem list and the 10th revision of the International Statistical Classification of Diseases billing codes entered by the clinician for the visit), the type of visit (new, returning, drop-in, or urgent care), the number of diagnostic tests related to the initial presentation ordered by the clinician within 30 and 90 days of the case presentation, and the number of unexpected visits related to the initial presentation (drop-in, urgent care, or emergency room) within 14 and 30 days of the index visit. We will use the same 2-investigator adjudication process to ascertain diagnostic tests and unexpected visits related to the initial presentation.

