### Case Selection Criteria

Scribes will select cases based on a rubric designed to capture diagnostic uncertainty. If a case meets any of the following criteria, it will be entered into the Human Dx platform: (1) a new symptom or abnormality in laboratory, physical exam, or radiographic finding; (2) a recurrent symptom or abnormality in laboratory, physical exam, or radiographic finding without a clear diagnosis or etiology; (3) a pending diagnostic test ordered to evaluate a new or unresolved condition; (4) empiric treatment provided without complete diagnostic certainty; and (5) if the clinician submitted a request for electronic consultation from a specialist within the health network for a diagnostic or management problem. Clinicians may also flag a case for review that the scribes will enter into the Human Dx platform whether or not it meets the above rubric’s selection criteria.

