**Figure 3 figure3:**
[figure not shown]
Study procedures. At baseline, clinicians are recruited and cases are collected and randomized to the intervention and control groups. Post-visit questionnaires will assess diagnostic confidence (the primary outcome) for each case. Exit interview sessions at 8 weeks will explore clinicians’ perception on usability. At 6-9 months, will conduct electronic medical record review to adjudicate clinic outcomes (secondary and exploratory outcomes).

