### Outcomes and Measurements

#### Primary and Secondary Outcomes

Our primary outcome will be self-reported diagnostic confidence as measured by response to the survey question in the postvisit questionnaire that asks participants after reviewing the collective intelligence output for cases randomized to the intervention group: “How confident do you feel about your diagnosis for this patient?” (Not at all, somewhat, moderately, and very). We chose this outcome based on previous literature in diagnostic safety suggesting that diagnostic confidence plays an important role in medical management, evolves over time in the process of making a diagnosis, and the ability to move diagnostic confidence may contribute to avoiding diagnostic error [18,19]. Furthermore, our preliminary studies for the proposed trial suggested that clinicians’ confidence in their clinical assessment is an important factor in their cognitive process for decision making and future approach to similar cases. We also chose this measure because it is likely the most sensitive to the impact of the collective intelligence on clinicians’ complex diagnostic decision-making process, whereas clinical outcomes such as *time to diagnosis* and diagnostic accuracy can be confounded by external health care system factors such as time to receive test results, financial incentives for diagnostic testing, and other factors. The secondary outcome will be *time to diagnosis*, defined as the interval between the time of the clinic visit from which a case with diagnostic uncertainty was identified for entry into the collective intelligence platform and the time at which the clinician will have established a diagnosis for that symptom or sign. We will ascertain the time of established diagnosis as the time at which the clinician documents the new diagnosis, the result for a confirmatory diagnostic testing becomes available, or empiric treatment was initiated. We will choose the earliest occurrence of any of these three events as the time of established diagnosis.

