#### Secondary Outcome

We will use Cox regression to compare time-to-diagnosis (T2Dx) between the intervention versus the control cases (ie, intervention status as primary predictor and T2Dx as outcome).

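### Dropping cases still undiagnosed at 6 months leaves no place for symptoms that resolve undiagnosed and, if applied to the Cox analysis, pulls a real time-to-diagnosis effect toward 1

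*Protocol article*

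**What the plan says.** Four parts of the protocol article bear on this point.

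- **Entry (Case Selection Criteria).** One qualifying feature is enough, for example "a new symptom or abnormality in laboratory, physical exam, or radiographic finding".
- **Event (Primary and Secondary Outcomes).** A diagnosis counts as established at "the time at which the clinician documents the new diagnosis, the result for a confirmatory diagnostic testing becomes available, or empiric treatment was initiated". The rule for several events is "We will choose the earliest occurrence of any of these three events as the time of established diagnosis".
- **Chart review (Electronic Health Record Chart Review).** Two investigators "independently review the medical record 6 months after the initial presentation of the case", and the purpose is "to ascertain the final diagnosis and exclude cases with persistent diagnostic uncertainty after 6 months". The Figure 3 legend gives a different time: "At 6-9 months, will conduct electronic medical record review to adjudicate clinic outcomes".
- **Analysis (Analysis Plan, Secondary Outcome).** "We will use Cox regression to compare time-to-diagnosis (T2Dx) between the intervention versus the control cases".

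The article does not say whether a settled symptom counts as persistent uncertainty, or which analyses the exclusion applies to.

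**The concern.** Some new symptoms seen in primary or urgent care go away without anyone naming a cause. If no label was recorded, no confirmatory test came back and no empiric treatment was started, the case never has the event. It is not clearly still uncertain either, because there is nothing left to diagnose. Two adjudicators could classify the same chart differently.

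The larger problem is the exclusion. Whether a case is diagnosed within 6 months is itself part of the outcome that the Cox model is meant to compare. Removing the undiagnosed turns the question from how fast cases reach a diagnosis into how fast the diagnosed cases reached theirs. An intervention that gets more cases diagnosed loses much of that advantage in such a comparison. What is at stake is the trial's only named secondary outcome.

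**Working it through.** **The plan's own figure.** None exists for time to diagnosis. The 660 cases (33 clinicians with 20 each) were sized for diagnostic confidence. I use 660 only to show what the bias does in a trial of that size.

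**Inputs.** From the article: the 6-month horizon, the exclusion and Cox regression. Assumed, because the article gives no rates: constant hazards, with diagnosis λ = 0.15 or 0.30 per month and undiagnosed resolution ρ = 0.10 or 0.20 per month in control. A second setting uses λ = 0.01 per day over 180 days.

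**What the exclusion does.** Among cases diagnosed by time τ, the diagnosis time is a truncated exponential with rate λ + ρ. Its hazard is

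h(t) = (λ + ρ) / [1 − exp(−(λ + ρ)(τ − t))].

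The treatment effect acts on λ only. Adding ρ dilutes it, and truncation at τ drives the ratio of the two hazards to 1 as t approaches τ.

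**True hazard ratio 1.5, same resolution rate in both arms** (λ = 0.30 versus 0.45, ρ = 0.20, τ = 6):
- Rates among the diagnosed: 0.50 versus 0.65, ratio 0.65/0.50 = 1.30.
- At t = 0: 0.50/(1 − e^−3.0) = 0.526 and 0.65/(1 − e^−3.9) = 0.663, ratio 1.26, falling to 1 at 6 months.
- Cox estimate in simulation: 1.22.

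Simulated Cox hazard ratios when the truth is 1.5:

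| λ control | ρ, both arms | Undiagnosed excluded | All kept, censored at resolution or 6 months |
|---|---|---|---|
| 0.15 | 0.10 | 1.12 | 1.51 |
| 0.15 | 0.20 | 1.12 | 1.49 |
| 0.30 | 0.10 | 1.23 | 1.50 |
| 0.30 | 0.20 | 1.22 | 1.50 |

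In the last row, with 660 cases and no clinician clustering, power falls from 99% to 49%.

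**No true effect, equal resolution.** The hazard ratio stays at 1.00 (0.995 to 1.003) under every handling tried. The exclusion alone creates no false signal.

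**No true effect, unequal resolution** (λ = 0.01 per day in both arms; ρ = 0.005 in control, 0.0075 in intervention):
- Share resolved undiagnosed by day 180, ρ/(λ + ρ) × [1 − e^(−180(λ + ρ))]: control 0.333 × (1 − e^−2.70) = 31%; intervention 0.429 × (1 − e^−3.15) = 41%.
- Diagnosed-only hazards at t = 0: 0.015/(1 − e^−2.70) = 0.0161 and 0.0175/(1 − e^−3.15) = 0.0183, ratio 1.14, falling to 1.
- Cox estimate: 1.11 with the undiagnosed excluded, 1.00 with censoring at resolution.

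With 660 cases, λ = 0.30 and ρ = 0.20 per month in control, and resolution 1.5 times as fast in intervention, excluding the undiagnosed rejects a true null in 24% of simulated trials. Censoring at resolution rejects in about 5%.

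**The case against.** **A condensed article.** Censoring and competing-event rules usually sit in a fuller plan, so their absence here is no fault. That stands. The exclusion, however, is stated, and it is the exclusion that does the damage. It may be meant only for diagnostic accuracy, which needs a final diagnosis to score against. The text does not limit it that way, so the point is conditional on its use in the Cox analysis.

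**Few cases may be affected.** A self-limited illness that was given a label or empiric treatment is already an event. That narrows the resolved-undiagnosed group, whose size is unknown. It does not help cases still unresolved at 6 months, which the exclusion also removes.

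**Stronger readings to avoid.**
- A reader might infer that resolved cases are counted as diagnostic failures. The article says nothing of the kind; the only stated fate of an undiagnosed case is exclusion. Keeping resolved cases at risk to 6 months would give about 0.84 in the 31% versus 41% setting, but the plan never states that rule.
- A reader might infer that the hazard ratio moves whenever symptoms resolve, even if diagnostic speed is unchanged. It does not. With no true effect, it moves only if undiagnosed resolution differs by arm.
- A reader might argue that the output's management plan leads clinicians to watch more cases until they settle, which would supply that difference. Watching in place of work-up mainly lowers the diagnosis hazard, so diagnostic speed has changed. With resolution held at 0.005 per day, a 41% resolved share arises if the intervention diagnosis hazard drops to 0.0053 per day. The true cause-specific ratio is then 0.0053/0.01 = 0.53, not 1.

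**Conclusion.** The point holds as a fault in a stated rule. The chart review recognises a final diagnosis or exclusion, gives undiagnosed resolution no category, and removes cases on a post-randomisation outcome. If the rule is applied to time to diagnosis, a true hazard ratio of 1.5 is reported as roughly 1.1 to 1.25, even with equal resolution rates. Under no effect there is distortion only if resolution differs by arm, for example about 1.11 with 31% versus 41% resolved.

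The sizes rest on assumed constant hazards, and the rejection rates ignore clinician clustering. The pull toward 1 with equal resolution rates appears in every setting tried. The outcome is secondary, and the Multiple Hypothesis Testing section treats it as exploratory. The article does not extend the exclusion to the primary confidence outcome. This should be corrected, but it does not threaten the main result.

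**What to change.** - State that cases undiagnosed at 6 months are **not** excluded from the time-to-diagnosis analysis, and keep all randomised cases in it. If the exclusion is meant for diagnostic accuracy only, say so.
- In the planned dual chart review, record one dated end state per case: diagnosed, resolved without a diagnosis, unresolved at 6 months, or last contact.
- Report the cause-specific hazard ratio for diagnosis, with censoring at resolution, last contact or 6 months. Add the cumulative incidence of diagnosis and of resolution by arm, so that any difference in resolution is visible.
- Reconcile the 6-month review in the text with the 6 to 9 months in the Figure 3 legend, so that every case has the same horizon.

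**Cost.** An end state and its date are added to a review that the plan already describes, plus a sentence or two on the Cox model. Some resolution dates will be approximate, and a chart cannot always separate resolution from no further contact.

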Once the collective intelligence output becomes available for a case, the study team randomizes it to the intervention or control cases. The study team assigned each case a unique study identification number for tracking purposes. Using a random number generator in blocks of four, we will randomize half of the cases, for each clinician, to an intervention group in which the clinician will receive a collective intelligence output between 60 and 80 hours from the time the clinician saw the patient in the clinic (ie, within 24-36 hours of case entry). For cases randomized to the controlled group, Human Dx will generate collective intelligence, but it will not be shared with the clinician. Clinicians will complete an online postvisit questionnaire for all of their cases (control and intervention) that provides their initial impressions of the case (eg, differential diagnosis and perceived case difficulty) and level of diagnostic confidence. The questionnaire for cases assigned to the intervention group includes additional questions that the clinician will answer after reviewing the collective intelligence output to assess the effect of the output on their diagnosis, plan, and confidence. The study scribes and the *contributors* on Human Dx will be blinded to case randomization.

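### Dropping cases still undiagnosed at 6 months makes the time-to-diagnosis comparison conditional on its own outcome

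*Protocol article*

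**What the plan says.** **Randomisation.** Cases are allocated early: "Once the collective intelligence output becomes available for a case, the study team randomizes it to the intervention or control cases". Allocation is within clinician: "we will randomize half of the cases, for each clinician, to an intervention group". In the intervention arm the clinician receives the output 60 to 80 hours after the visit.

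**Exclusion.** The section on electronic health record chart review has two investigators read the record 6 months after presentation to "ascertain the final diagnosis and exclude cases with persistent diagnostic uncertainty after 6 months". It does not name the analyses to which this applies.

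**Reach of the review.** The Figure 3 legend says the study team "will conduct electronic medical record review to adjudicate clinic outcomes (secondary and exploratory outcomes". T2Dx is the only secondary outcome. Tests within 30 and 90 days, unexpected visits within 14 and 30 days, and diagnostic accuracy are exploratory.

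**Analysis.** For the secondary outcome: "We will use Cox regression to compare time-to-diagnosis (T2Dx) between the intervention versus the control cases". The T2Dx endpoint is the documented diagnosis, or "the result for a confirmatory diagnostic testing becomes available, or empiric treatment was initiated", and "We will choose the earliest occurrence of any of these three events as the time of established diagnosis".

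**The concern.** Whether a case is resolved by 6 months is a result that follows randomisation, not a baseline feature. If the output helps clinicians reach a diagnosis, fewer intervention than control cases will still be uncertain at 6 months, so the rule removes unequal shares of the two arms. T2Dx is then compared only among cases that were resolved.

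Cox regression does not need this. A case without an event contributes its follow-up time as a censored observation, and that is where much of the difference between the arms lies. Tests and visits do not need it either: they are counted in windows that close by 90 days and require no final diagnosis.

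At stake is the interpretation of the only secondary outcome. A real effect could be reported as small or absent or, under some effect patterns, with the wrong size or sign.

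**Working it through.** **Inputs from the article.** 33 clinicians × 20 cases = 660 cases, so 330 per arm at 1:1. Review is at 6 months and the model is Cox. The article states no hazard ratio, event count or power for T2Dx, so there is no T2Dx figure to reproduce.

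**Assumptions.** The share u of control cases unresolved at 6 months is 10% to 50%. True hazard ratios θ are 1.50 and 1.25. Times are exponential and two-sided alpha is 0.05. Clinician clustering is ignored. For this calculation, unresolved means having no T2Dx event by 6 months; the limits of that are taken up under the objection.

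**Step 1: unequal removal.** Under proportional hazards the unresolved share in the intervention arm is u^θ. With u = 0.30 and θ = 1.50 this is 0.30^1.5 = 0.164. The rule removes 30% of control and about 16% of intervention cases, leaving 330 × 0.70 = 231 and 330 × 0.836 ≈ 276.

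**Step 2: hazard ratio after exclusion.** Let v(t) = S0(6 months)/S0(t), where S0 is the control survival function. Among resolved cases the hazard ratio at time t is

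HR(t) = θ(1 − v)/(1 − v^θ).

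At t = 0, v = u. For u = 0.30 and θ = 1.50 this gives 1.50 × 0.70/0.836 = 1.26. As t approaches 6 months, v approaches 1 and HR(t) approaches 1. For any θ other than 1, the value lies between 1 and θ throughout. The Cox estimate averages over this curve.

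**Step 3: large-sample Cox estimate.**

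| Control cases unresolved | θ = 1.50, excluded | θ = 1.25, excluded | Either θ, event-free cases censored |
|---|---|---|---|
| 10% | 1.31 | 1.15 | θ recovered |
| 20% | 1.22 | 1.11 | θ recovered |
| 30% | 1.17 | 1.08 | θ recovered |
| 50% | 1.09 | 1.04 | θ recovered |

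**Step 4: approximate power.** Power = Φ(|ln HR| × √(D·p(1 − p)) − 1.96), where D is the number of events. With censoring p = 0.5; after exclusion p is the intervention share of the cases kept. At u = 0.30 and θ = 1.50, D = 231 + 276 = 507:
- Censored: 0.405 × √(507/4) − 1.96 = 2.60, power above 99%.
- Excluded: ln 1.165 = 0.153 and p = 276/507 = 0.544, so 0.153 × √(507 × 0.248) − 1.96 ≈ −0.25, power about 40%.

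Both analyses use the same events, so the loss comes from the shrunken contrast. For θ = 1.25 at u = 0.30, power falls from about 69% to 13%. For θ = 1.50 it is about 91% after exclusion at u = 0.10 and 66% at u = 0.20.

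**Step 5: effect patterns without proportional hazards.**
- The intervention only speeds up diagnosable cases, with 30% never diagnosed in both arms: the all-cases hazard ratio of about 1.14 becomes about 1.48, further from 1.
- It only lowers the never-diagnosed share from 30% to 20%, with timing unchanged: about 1.28 becomes 1.00.
- It lowers that share, but the extra diagnoses come late: about 1.20 becomes about 0.91, crossing 1.
- Strict null: 1.00 stays 1.00.

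**The case against.** Several stronger readings are tempting, and the article does not support them.

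**That the rule removes exactly the censored cases.** It does not. Starting empiric treatment is a T2Dx event, and one of the case selection criteria is "empiric treatment provided without complete diagnostic certainty". A case can therefore have an event, possibly at the index visit, still be uncertain at 6 months, and be excluded. Conversely, a case lost to follow-up would be censored without being judged persistently uncertain. The two sets overlap but differ, so the figures above illustrate the mechanism and do not predict this trial's result.

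**That the bias is always toward 1.** This is assured only for a non-null effect under proportional hazards, as Step 5 shows.

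**That most of the power is always lost.** At a hazard ratio of 1.50 with 10% unresolved, about 91% remains.

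**That the primary comparison is broken.** A reader might infer this because the exclusion has no stated scope. But confidence comes from the postvisit questionnaire, its analysis section names no such exclusion, and the chart review is linked to the secondary and exploratory outcomes.

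It is also fair to say that the article treats secondary analyses as hypothesis generating, and that a censoring rule may properly sit in a fuller plan. Both points stand, and the first limits the severity. Neither removes the finding, which rests on an exclusion that is stated and not on an omission. The planned multiple imputation does not help, because an excluded case is not a missing value.

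For diagnostic accuracy, an exclusion is defensible because there must be a final diagnosis to compare with. Scoring unresolved cases as incorrect is open to dispute: if more control cases are unresolved, it would favour the intervention.

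**Conclusion.** The concern holds for T2Dx and for the test and visit counts. As written, these are compared on cases selected after randomisation by the process under study.

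Under proportional hazards and an assumed 10% to 50% of control cases unresolved, a true hazard ratio of 1.50 is estimated at about 1.31 down to 1.09, and one of 1.25 at about 1.15 down to 1.04. Power falls with it. Outside proportional hazards the direction is not assured, which is a further reason not to condition on resolution.

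The size rests on unresolved rates and hazard ratios that the article does not give, on treating unresolved cases as event-free, and on ignoring clinician clustering. The primary outcome is not shown to be affected. Severity: should fix, on a secondary outcome.

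**What to change.** - State that the exclusion does not apply to T2Dx, tests or visits, and keep every randomised case in its allocated arm for these.
- In the Cox model, count any event that meets the article's T2Dx definition, and censor only event-free cases, at 6 months or at the last record if earlier.
- Limit the exclusion to diagnostic accuracy. Report the number excluded in each arm and add a sensitivity analysis on how unresolved cases are counted.
- Reconcile the outcome definition with the chart-review rule for cases that have an empiric-treatment event but are still uncertain at 6 months, so that both sections treat them alike.

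The cost is a change of wording. The same chart review supplies the event and censoring dates, and no further data are needed.

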### Analysis Plan

#### Primary Outcome

We will perform a bivariate logistic regression with the intervention status (clinician access to collective intelligence output vs no access to collective intelligence) as the predictor and diagnostic confidence as the outcome, clustering on clinician. Self-reported diagnostic confidence will be treated as a categorical variable with “not at all” as the reference group.

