#### Exploratory Analyses

We will perform mixed-effect multivariable logistic regressions to compare diagnostic confidence, T2Dx, and diagnostic accuracy of intervention versus control cases, accounting for clustering by clinician and adjusted for baseline diagnostic uncertainty, perceived case difficulty, patient age, race, gender, number of comorbid conditions, type of visit (new, returning, drop-in, or urgent care), and primary care clinician characteristics such as professional degree (NP vs MD), specialty (family vs internal medicine), and years of experience. We have chosen covariates a-priori based on clinical judgment. For cases randomized to the intervention, mixed-effect bivariate logistic regressions will compare physicians’ diagnostic accuracy before and after reviewing the collective intelligence, adjusted for the aforementioned clinician characteristics. We will use bivariate and multivariable linear regressions to compare the number of diagnostic testing and use logistic regressions to compare the occurrence of unexpected clinical visits at 30 days between intervention versus control cases.

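### The primary model omits case variables that are fixed at the index visit and already chosen in advance; adjusting for them is a cheap, modest gain in precision, not the repair of an error

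*Protocol article*

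**What the plan says.** All references are to the Protocol article.

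- **Analysis Plan, Primary Outcome.** "We will perform a bivariate logistic regression with the intervention status" "as the predictor and diagnostic confidence as the outcome, clustering on clinician". No case-level covariate enters.
- **Exploratory Analyses.** "We will perform mixed-effect multivariable logistic regressions to compare diagnostic confidence, T2Dx, and diagnostic accuracy of intervention versus control cases". These models account for clinician and are "adjusted for baseline diagnostic uncertainty, perceived case difficulty, patient age, race, gender, number of comorbid conditions, type of visit", together with clinician degree, specialty and experience. On the choice of variables: "We have chosen covariates a-priori based on clinical judgment".
- **Selection, Entry, and Randomization of Clinical Cases.** "Once the collective intelligence output becomes available for a case, the study team randomizes it to the intervention or control cases". Allocation is 1:1 within clinician in blocks of four. The questionnaire is one "that provides their initial impressions of the case (eg, differential diagnosis and perceived case difficulty) and level of diagnostic confidence".
- **Postvisit Questionnaires.** The questionnaire goes out after allocation. For intervention cases the same email carries the link to the output, and the order of answering rests on instructions.
- **Electronic Health Record Chart Review.** Visit type and comorbidity count are abstracted at a review six months after presentation. The count uses the problem list and the billing codes entered for the visit.
- **Sample Size Justification.** 33 clinicians with about 20 cases each (660 cases), 80% power, a 20% difference, within-clinician correlation 0.3.

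**The concern.** Cases are randomised within clinician, so the treatment contrast rests on variation between cases of the same clinician. Clustering on clinician, or adding clinician degree, specialty or experience, does almost nothing to that variation. Only case-level covariates can reduce it. The investigators have judged several such variables relevant in advance and will hold them anyway, yet the confirmatory test uses none.

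The one adjusted model of confidence does not fill the gap. It includes perceived case difficulty, which the clinician rates after allocation, with the output one click away in the intervention arm. It also includes baseline diagnostic uncertainty. No source is given for that item, but the only place where the article describes collecting initial impressions is the same questionnaire. At stake is some precision in the primary comparison, and a clean adjusted estimate to set beside the unadjusted one.

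**Working it through.** **1. Which covariates precede randomisation?** The visit comes first, then the scribe's review and case entry, then the output, then randomisation.

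| Variable | Fixed before allocation? |
|---|---|
| Patient age, race, gender, visit type | Yes |
| Billing codes for the visit | Tied to the visit |
| Problem list | Only if restricted by date; it is read at six months |
| Perceived case difficulty | No; questionnaire item |
| Baseline diagnostic uncertainty | Apparently not; see above |
| Clinician degree, specialty, experience | Yes, but constant within clinician |

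**2. The plan's own figure.** Control rate and alpha are not stated. I take two-sided 0.05 and read 20% as 20 percentage points. For 25% v 45%, with mean 0.35:

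n per arm = [1.96·√(2·0.35·0.65) + 0.842·√(0.25·0.75 + 0.45·0.55)]² / 0.20² = 88.1, so 89.

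Design effect for 10 cases per arm per clinician: 1 + (10 − 1)·0.3 = 3.7. Clinicians: 89·3.7/10 = 32.9, so 33. The figure reproduces. Control rates of 20–30% or 50–60% give 31–35 clinicians; 35–45% gives 36.

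**3. The design actually used.** With both arms inside each clinician, the variance factor is 1 − 0.3 = 0.7, and the effective number per arm is 330/0.7 = 471. Power for 20 points is then above 99.9% with or without covariates. From a 40% control rate, the difference detectable at 80% power is 9.1 points unadjusted, 8.6 if covariates explain 10% of outcome variance, and 8.1 if they explain 20%.

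**4. Approximate gain.** Divide the variance by multiplying effective n by 1/(1 − R²), where R² is the assumed share of outcome variance explained:

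| R² | 25% v 45%, factor 3.7 | 40% v 60%, factor 3.7 | 40% v 50%, factor 0.7 |
|---|---|---|---|
| 0 | 80.5% | 76.6% | 87.1% |
| 0.05 | 82.5% | 78.7% | 88.7% |
| 0.10 | 84.5% | 80.9% | 90.3% |
| 0.20 | 88.4% | 85.3% | 93.3% |

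The first two columns use the plan's apparent sizing basis, which ignores the within-clinician contrast. The third uses the actual design at half the planned difference.

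**5. Simulation of the actual design.** 33 clinicians × 20 cases, blocks of four, latent intraclass correlation 0.3, binary outcome, one case covariate, clinician-clustered logistic regression, true difference about 9–10 points. Power, unadjusted then adjusted (read across the rows):

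| Within-clinician latent variance explained | 2,000 runs | 3,000 runs |
|---|---|---|
| 5% | 83 → 84% | not run |
| 10% | 80 → 83% | 82.0 → 84.4% |
| 20% | 74 → 78% | 77.4 → 82.1% |
| 30% | 67 → 74% | 70.3 → 79.1% |

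For 5–20% the gains run from 1 point (84 − 83) to 4.7 points (82.1 − 77.4). Type I error was 4–6% in one set and 5–6% in the other, for both models. A small check with 200 runs per setting, using generalised estimating equations, gave 75 → 77% at about 5% explained and 70 → 76.5% at about 16%. The Monte Carlo standard error of one such figure is √(0.7·0.3/200) = 3.2 points, so it supports the direction only. At about 20 points it gave 100% both ways.

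**The case against.** The strongest reply is that nothing here is wrong. The primary test is valid, it accounts for clinician, and an adjusted model with pre-chosen covariates is also planned. **That stands:** this is an improvement, not a defect.

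Second, a gain on the actual design appears only at about half the planned difference, and the explained share is assumed. Once the questionnaire items are excluded, the likely strongest predictors are gone, and age, visit type and comorbidity may predict confidence only weakly. **This stands too,** and it puts the low end of the range in play.

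Third, a problem list read at six months may hold diagnoses added after randomisation, some perhaps prompted by the output. **This stands,** and it is why the count must be restricted by date.

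Fourth, the simulation used a binary outcome and one covariate. Age, the count and a four-level visit type need 1 + 1 + 3 = 5 coefficients. If confidence is modelled in its four categories, as the Primary Outcome text suggests, that becomes 5 × 3 = 15. The cost was not simulated. It argues for a short covariate list and for settling the form of the outcome first.

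A reader might also infer more than the document supports:

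- *That the unadjusted odds ratio is biased toward 1.* The shift is non-collapsibility: marginal and conditional odds ratios are different estimands.
- *That the confirmatory test is simply the weaker of two analyses the trial will run anyway.* The planned adjusted model contains post-allocation ratings, so it is not the model simulated here.
- *That the visit lies 60–80 hours before randomisation.* That interval runs from the visit to the clinician's receipt of the output. The visit still comes first, which is all the point needs.

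**Conclusion.** The point holds as a low-cost precision improvement. The primary model is valid but leaves out case-level variables fixed at the index visit and already named in advance. The only adjusted model of confidence mixes them with a rating made after allocation.

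The size is modest: about 1 to 5 points of power at a true difference of 9 to 10 points if the covariates explain 5–20% of within-clinician variance, and essentially nothing at 20 points on the within-clinician design. This rests on an undocumented prognostic strength, an unstated control rate, an assumed two-sided alpha of 0.05, and a binary outcome. No setting examined showed a loss of power or a material rise in type I error. The document does not support a claim that the trial is underpowered or its primary estimate biased because of this omission.

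**What to change.** Reword the Primary Outcome analysis so that the logistic model accounts for clinician and adjusts for patient age, visit type and comorbidity count. Define the count from billing codes for the index visit and problem-list entries dated on or before it. Leave perceived case difficulty and baseline diagnostic uncertainty out of this model. Report the unadjusted model as a sensitivity analysis, and give a standardised risk difference with its 95% CI beside the conditional odds ratio. Fix the wording before confidence is examined by arm.

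Cost: no new variables, only a date check on problem-list entries at chart review. The analysis pays with a few extra coefficients and an odds ratio that becomes conditional, which the standardised difference answers. The multiple imputation already planned can cover missing covariate values.
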